## Abstract

**Background:**

Oral Potentially Malignant Disorders (OPMD) have a non-negligible malignant transformation rate of up to 8%. Loss of heterozygosity (LOH) in critical chromosomal loci has proven to be the most effective marker in defining the risk of transformation and it is found in about 28% of OPMD and may therefore identify patients carrying higher risk. To date, clinical management of OPMD is limited to surgical excision and clinical surveillance, which however do not fully prevent oral cancer development. Immune system has been shown to play a key role in transformation surveillance mechanism and an immunosuppressive imbalance may be responsible for progression to cancer. Given all these considerations, we designed a clinical trial with the aim to prevent OPMD neoplastic transformation and revert the LOH status.

**Methods:**

This is a phase II, open label, single arm, multicentric trial involving Italian referral centres and expected to enrol 80 patients out of a total of 175 screened. Patients who meet all inclusion criteria and test positive for LOH after an incisional biopsy of the OPMD will undergo a short course of immunotherapy with 4 administration of avelumab. After 6 months since treatment start, resection of the entire OPMD will be performed and LOH assessment will be repeated. The follow-up for malignant transformation and safety assessment will last 30 months from the end of treatment, for a total planned study duration of approximately 5.5 years.

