## Background

Oral Potentially Malignant Disorders (OPMD) represent the most common oral precancerous condition, with an estimated prevalence rate worldwide of 4.5% [1] and, according to a recent meta-analysis, an overall potential of neoplastic transformation of 7.9% [2].

Among molecular markers, the most effective in predicting the risk of progression to oral cancer is loss of heterozygosity (LOH), which may appear in tissues regardless of their histological grade of dysplasia [3, 4]. This chromosomal profile may be found in about 28% of OPMD [5]. Patients carrying OPMD with LOH at 3p14 and/or 9p21 plus LOH at another locus have an expected 3-year risk of developing oral cancer of 35%. Moreover, when a patient previously suffered from oral cancer, the 3-year risk of malignant transformation for OPMD with defined LOH reaches 69% [6]. The presence of tumour suppressor genes at these chromosomal loci explains the potential for cancer development in presence of such alterations.

The clinical management of small OPMD is excision by electrocautery or laser. However, treatment is not always effective in preventing oral cancer. Lesions recur frequently and may subsequently progress, with tumours developing in the same or adjacent anatomical regions [7]. For larger OPMD, clinical management may be limited to lifelong surveillance as an alternative to potentially morbid repeated, multi-step surgical treatments. To improve clinical care of OPMDs, the arsenal of treatments should be expanded.

OPMD may be considered as the equilibrium phase of the immunoediting concept, i.e. a dynamic process between the tumour cells and the immune system including immunosurveillance or tumour progression [8, 9]. Thus, an imbalance in the immunosuppressive microenvironment is a possible key for malignant transformation. In this regard, the activation of the PD-1/PD-L1 pathway has a central role, witnessed by the expression of PD-L1 by multiple cell types within the OPMD microenvironment (tumour-associated macrophages, fibroblasts, lymphocytes), and by the fact that PD-L1 expression in epithelial and subepithelial cells is associated with malignant transformation [10]. The use of checkpoint inhibitors in this setting is justified by this rationale.

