## Methods and design

### Objectives

#### Primary objective

The primary objective is to revert the risk of malignant transformation of OPMD through a short course of immunotherapy with avelumab, a *PD-L1*-blocking monoclonal antibody agent. This objective will be evaluated both with an intermediate endpoint (restore of LOH status) and in its final endpoint (malignant transformation).

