**Fig. 1 Fig1:**
[figure not shown]
Study design

The first study phase of screening begins by establishing the subject’s initial eligibility and signing of the informed consent form (ICF). Patients who choose to participate in the study will then undergo an incisional biopsy of the OPMD and, only in case of dysplasia (regardless of grading), will be included in this study and test for LOH.

LOH negative subjects who meet all other inclusion criteria, will be treated as per clinical practice (e.g., OPMD surgical excision and/or follow-up). However, information on the malignancy free-survival period will be collected for these patients at 30 months from the end of the screening phase.

LOH positive subjects will then undergo a short course (4 cycles) of immunotherapy with avelumab flat dose (800 mg iv) every 2 weeks. Four administrations of the checkpoint inhibitor avelumab have been chosen with the rationale to induce a response in lesions whose immunological derangement is expected to be less severe than in advanced cancer [10]. According to the immunoediting concept, OPMD are considered in the equilibrium phase, but the discovery of high-risk LOH could represent the initial step of immunoescape; therefore, a short course of immunotherapy could be considered sufficient to reverse such a shift in immunocompetence. Moreover, a limited number of administrations could expose patients to less risk of adverse events. This period of treatment is also consistent with other preventive trials in OPMD, both with targeted agents (cetuximab for 2 months, according to Khan et al. [11]) and immunotherapy (pembrolizumab for 4 cycles, clinicaltrials.gov: NCT02882282).

After 6 months since treatment start, excisional biopsy of OPMD will be performed or, in case of not feasibility or excessive potential morbidity of a complete resection, another incisional biopsy will be performed and LOH assessment repeated. In case of complete clinical response, the site of previous OPMD will be biopsied, to define histology and to assess LOH even in presence of normal mucosa. The 6-month timeframe to assess changes in LOH has been chosen because it is relevant for the immune system to produce a shift in genetic markers and it is a period that may be consistent with clinical practice when re-assessing a lesion for surgery.

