### Statistical analysis

The first coprimary endpoint is the recurrence or malignancy-free survival, for which the time is the interval from the date of the start of immunotherapy to the date of recurrence of OPMD with LOH or of malignant transformation or the date of death without recurrence/malignancy (if caused by treatment), whichever will occur first. Time will be censored at the date of last follow-up for patients alive and without events or dead for causes not related to the treatment. The recurrence or malignancy-free survival curve will be estimated with the Kaplan-Meier method.

The second co-primary endpoint is the change in LOH status (positive to negative) after 6 months of treatment with immunotherapy. The probability of change in LOH status after 6 months of treatment will be estimated with the corresponding relative frequency of patients with change among the total number of LOH positive patients at treatment start; the corresponding exact Clopper-Pearson 95% confidence interval will be estimated.

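### The survival co-primary runs through the default month-6 excision in a single arm, so it measures avelumab plus surgery and cannot be credited to avelumab alone

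*Protocol article*

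**What the plan says.** - **Design (Abstract, Methods):** "This is a phase II, open label, single arm, multicentric trial involving Italian referral centres". There is no concurrent control.
- **Objective (Primary objective):** "The primary objective is to revert the risk of malignant transformation of OPMD through a short course of immunotherapy with avelumab". The same section names malignant transformation as the final endpoint for that objective.
- **Month-6 procedure (Abstract, Methods):** "After 6 months since treatment start, resection of the entire OPMD will be performed and LOH assessment will be repeated". No exception is given there.
- **Month-6 procedure (Study design):** excision is the default, but "in case of not feasibility or excessive potential morbidity of a complete resection, another incisional biopsy will be performed". Also: "In case of complete clinical response, the site of previous OPMD will be biopsied".
- **Survival clock (Statistical analysis):** "the interval from the date of the start of immunotherapy to the date of recurrence of OPMD with LOH or of malignant transformation". Treatment-related death also counts as an event.
- **Follow-up (Abstract, Methods):** 30 months from the end of treatment.
- **Test (Sample size determination, Table 2):** a one-sample log-rank test at 2.5% against a fixed 3-year S0. Eight candidate values from 0.30 to 0.65 are listed, none described as coming from excised patients.
- **Existing care (Background):** "The clinical management of small OPMD is excision by electrocautery or laser". The section adds that this does not always prevent cancer, and that larger lesions may only be kept under surveillance.

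**The concern.** The protocol schedules a second, potentially preventive intervention inside the survival window and then reads the whole window as the effect of the first. With no control arm, only S0 could remove the contribution of surgery, and the article does not say that S0 reflects it.

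The endpoint definition adds to this. A lesion still LOH-positive at month 6 is not a recurrence, a transformation or a death. If it is then excised and does not return, a patient in whom avelumab changed nothing counts as a survival success.

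At stake is the reading of one of two co-primaries. A positive test would be reported as avelumab reverting the risk of oral cancer, when the design supports only a statement about avelumab followed by surgery.

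**Working it through.** **The plan's own figures.** Screening reproduces: 28/0.28 + 52/0.69 = 175. Table 2 does not reproduce at its stated inputs. Take S0 = 0.45 and S1 = 0.67: HR = ln 0.67/ln 0.45 = 0.50, events d = (1.960 + 0.842)²/(ln HR)² = 16.5, event probability 0.232 under 2 years' accrual plus 1 year, so N = 72 against the stated 78. Across the rows the formula gives 70 to 75 against 78 to 83. An unstated 10% dropout would close the gap. The stated N is conservative, and this neither supports nor weakens the present point.

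**Share of the window after surgery.** Four doses every 2 weeks put the last dose at week 6, about 1.4 months. Adding 30 months gives month 31.4 (31.8 if treatment is taken to end at week 8). Then (31.4 − 6)/31.4 = 25.4/31.4 = 81%.

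**A null survival for illustration.** The Background gives 3-year cancer risks of 35% and 69%, so survival of 0.65 and 0.31. With the planned 28 and 52 patients, (28 × 0.65 + 52 × 0.31)/80 = 0.43. This is an assumption: the plan fixes no S0, and these risks count cancer only.

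**Inert drug, with surgery that lowers the later hazard.** Assume a constant null hazard −ln(S0)/36 per month up to month 6, then the same hazard times h in excised patients. With everyone excised,

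S(36) = exp{ln(S0) × (6/36 + 30/36 × h)}.

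For S0 = 0.43, h = 0.7, 0.5 and 0.4 give 0.53, 0.61 and 0.66. These are gains of about 10, 18 and 23 points; Table 2 looks for 20 to 22.

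**False-positive rate.** Simulated trials with N = 80, rejecting when (O − E)/√E < −1.96. O and E are the observed and expected events. S0 = 0.43; repeat runs differ by about one point.

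| h after surgery | All excised, to month 31.4 | All excised, 2+1 years | Half excised, to month 31.4 | Half excised, 2+1 years |
|---|---|---|---|---|
| 1.0 | 2% | 2% | 2% | 2% |
| 0.7 | 32% | 22% | 10% | 8% |
| 0.5 | 78% | 59% | 26% | 18% |
| 0.4 | 93% | 78% | 37% | 26% |

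With everyone excised and h = 0.5, S0 = 0.65 gives 55% (month 31.4) or 37% (2+1 years), and S0 = 0.30 gives 86% or 69%.

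**Surgery needed to reach S1 by itself.** Solving the formula for h, with HR = ln S1/ln S0, gives h = (HR − 1/6)/(5/6). This is 0.49 for S0 = 0.30, 0.40 for S0 = 0.45 and 0.19 for S0 = 0.65. At the high end of Table 2, surgery would have to be very effective to deliver the whole planned difference.

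**The case against.** The strongest reply is that surgery may already be in the benchmark. The Abstract describes current management as excision and surveillance, and Study design calls the 6-month interval consistent with practice when a lesion is reassessed for surgery. If the patients behind S0 were excised as usual care, the bias shrinks or disappears and the error rate returns to about 2%. That stands as a possibility. The article does not say, so it cannot be relied on either.

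Three further replies have force:

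- **Not everyone will be excised.** Eligibility requires a diameter of at least 20 mm, and the Background says larger lesions may only be watched. A reader of the Abstract might infer that every patient is resected; Study design does not support that. Hence the half-excised columns.
- **The excision effect has no source.** The Background says lesions recur often and that tumours arise in the same or adjacent regions, which does not suggest a large effect. The higher rates in the table are conditional illustrations.
- **The endpoint also counts recurrence of OPMD with LOH.** Set against a cancer-only S0, the extra events make a false positive less likely.

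None of these restores attribution to avelumab. They limit what can be said about the direction and size of the bias.

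**Conclusion.** The point holds in a limited form. From the text alone, one arm, a clock from first dose, default excision at month 6 and a fixed S0 not tied to excised patients mean that the survival co-primary cannot separate drug from surgery, yet the objective credits the drug.

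The size of any bias is conditional. With S0 = 0.43, N = 80 and assumed hazard ratios of 0.7 to 0.4, the false-positive rate runs from about 8% (half excised, 2+1 years) to about 93% (all excised, month 31.4). It is about 2% if excision adds nothing beyond S0.

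Two stronger readings are tempting. One is that the test is bound to favour avelumab: this does not follow, because it requires surgery to lower the hazard below the one behind S0, and the documents give neither quantity. The other is that both co-primaries are compromised: change in LOH is read on the month-6 tissue itself, so the surgery does not confound it.

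**What to change.** 1. In Primary objective and Statistical analysis, state that the survival co-primary evaluates avelumab followed by month-6 excision where feasible (in the terms settled under item 4), and that a positive test supports that strategy, not avelumab alone.
2. In Sample size determination, require S0 to come from LOH-positive patients with comparable surgical management and the same event definition. Name the source and fix the value before outcome data are read.
3. Report separately, and only descriptively, cancers diagnosed before the month-6 procedure and cancers first found in its specimen. The latter may have been missed by the baseline incisional biopsy.
4. Reconcile the Abstract with Study design on who is resected at month 6.

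A landmark analysis split by procedure performed is not recommended as a remedy. The procedure depends on response and resectability, so its groups are selected after treatment and would not isolate the drug.

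The cost is wording, one benchmark justification and a small descriptive table from follow-up already planned. Treatment and patient numbers are not changed by the wording; a different S0 would need a check against Table 2. The downside is a narrower claim for avelumab.

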**Discussion:**

Restoring the activity of immune system through checkpoint inhibitor may play a crucial role against malignant transformation of OPMD by reverting the balance in favour of immune control and preventing cancer occurrence.

**Trial registration:**

This trial was prospectively registered in ClinicalTrials.gov as NCT04504552 on 7th August 2020.

**Supplementary Information:**

The online version contains supplementary material available at 10.1186/s12885-021-08297-3.

## Background

Oral Potentially Malignant Disorders (OPMD) represent the most common oral precancerous condition, with an estimated prevalence rate worldwide of 4.5% [1] and, according to a recent meta-analysis, an overall potential of neoplastic transformation of 7.9% [2].

Among molecular markers, the most effective in predicting the risk of progression to oral cancer is loss of heterozygosity (LOH), which may appear in tissues regardless of their histological grade of dysplasia [3, 4]. This chromosomal profile may be found in about 28% of OPMD [5]. Patients carrying OPMD with LOH at 3p14 and/or 9p21 plus LOH at another locus have an expected 3-year risk of developing oral cancer of 35%. Moreover, when a patient previously suffered from oral cancer, the 3-year risk of malignant transformation for OPMD with defined LOH reaches 69% [6]. The presence of tumour suppressor genes at these chromosomal loci explains the potential for cancer development in presence of such alterations.

The clinical management of small OPMD is excision by electrocautery or laser. However, treatment is not always effective in preventing oral cancer. Lesions recur frequently and may subsequently progress, with tumours developing in the same or adjacent anatomical regions [7]. For larger OPMD, clinical management may be limited to lifelong surveillance as an alternative to potentially morbid repeated, multi-step surgical treatments. To improve clinical care of OPMDs, the arsenal of treatments should be expanded.

OPMD may be considered as the equilibrium phase of the immunoediting concept, i.e. a dynamic process between the tumour cells and the immune system including immunosurveillance or tumour progression [8, 9]. Thus, an imbalance in the immunosuppressive microenvironment is a possible key for malignant transformation. In this regard, the activation of the PD-1/PD-L1 pathway has a central role, witnessed by the expression of PD-L1 by multiple cell types within the OPMD microenvironment (tumour-associated macrophages, fibroblasts, lymphocytes), and by the fact that PD-L1 expression in epithelial and subepithelial cells is associated with malignant transformation [10]. The use of checkpoint inhibitors in this setting is justified by this rationale.

Employing intermediate end-point markers during preventive strategies against OPMD may allow the conduction of smaller trials, able to give insights for designing larger ones and to better select the population receiving benefit from a given treatment. In this regard, the evaluation of phenotypic changes (reduction in size or in grade of dysplasia) may not be enough to assess the potential benefit of an intervention. Modulation of molecular markers may be in fact a more precise indicator of oral cancer risk in patients with OPMD. Thus, the change in LOH in critical loci may be considered an intermediate end-point biomarker of prevention, as well as a predictor of cancer risk at baseline. Previous experience with anti-EGFR agent showed the feasibility of such measures in a prevention trial [5].

## Methods and design

### Objectives

#### Primary objective

The primary objective is to revert the risk of malignant transformation of OPMD through a short course of immunotherapy with avelumab, a *PD-L1*-blocking monoclonal antibody agent. This objective will be evaluated both with an intermediate endpoint (restore of LOH status) and in its final endpoint (malignant transformation).

#### Secondary objectives

To evaluate the safety of an immunotherapeutic approach in OPMDTo assess the change of histological grade of OPMDTo discover genomic predictive tools able to foresee response to avelumab

### Endpoints

#### Co-primary endpoints

Recurrence or malignancy-free survival since the start of immunotherapy, for which the events of interest are the recurrence of OPMD with LOH or malignant transformationChange in LOH status (positive to negative) of OPMD after 6 months since the start of avelumab. This is defined as the disappearance of any high-risk LOH (and the non-appearance of any other high-risk LOH) in the histological exam of the OPMD after immunotherapy treatment

#### Secondary endpoints

Grade 3–5 adverse events or any treatment interruption due to toxicities (safety)Change of histological grading of OPMDIdentification of multi-omics signatures associated with response to immunotherapy

### Patient population and eligibility criteria

#### Inclusion criteria

Signed written informed consent;Male or female > 18 years of age;ECOG Performance status (PS) 0–1;Clinical and histological evidence of OPMD without prior history of oral cancer and with high risk of malignant transformation as defined by LOH at 3p14 and/or 9p21 plus at least in one additional chromosomal site (4q, 8p,11q,13q, or 17p), or patients with a prior oral cancer history and LOH at 3p14 and/or 9p21 (LOH defined according to EPOC trial [5]). These conditions define the “LOH positivity”;OPMD with a histological definition of dysplasia and a diameter of at least 20 mm;Willing to provide tissue from newly obtained oral biopsies;Not receiving chronic systemic steroidal therapy or any immunosuppressive therapy within 7 days prior to the first treatment;Absence of active autoimmune disease that required systemic treatment in the past 2 years;Adequate bone marrow function: neutrophils > 1.5 × 10^9^/L, platelets > 100 × 10^9^/L, haemoglobin > 9 g/dL;Adequate liver function: bilirubin < 2 times above the upper normal limit (except known medical reasons not interfering with liver function, such as Gilbert disease), AST, ALT, ALP, GGT < 3 times above the upper normal limits;Adequate renal function: calculated or analysed creatinine clearance > 60 mL/min;If of childbearing potential, willingness to use effective contraceptive method (Pearl Index < 1; e.g. oral contraceptive [pill], hormone spiral, hormone implant, transdermal patch, a combination of two barrier methods [condom and diaphragm], sterilization, sexual abstinence) for the study duration and 2 months post-dosing.

#### Exclusion criteria

Previous immunotherapy (anti-PD-1, anti-PD-L1, anti-PD-L2, anti-CTLA-4 antibody or any other antibody or drug specifically targeting T-cell co-stimulation or immune checkpoint receptors);Biopsy-proven oral lichen planus;Diagnosis of prior immunodeficiency or organ transplant requiring immunosuppressive therapy, or known human immunodeficiency virus (HIV) or acquired immunodeficiency syndrome (AIDS)-related illness;Any test for hepatitis B virus (HBV) or hepatitis C virus (HCV) indicating acute or chronic infection;Vaccination within 4 weeks of the first dose of avelumab and while on trial is prohibited except for the administration of inactivated vaccines (for example, inactivated influenza vaccines);Clinically significant cardiovascular disease, e.g. cardiac failure of New York Heart Association classes III-IV, uncontrolled coronary artery disease, cardiomyopathy, uncontrolled arrhythmia, uncontrolled hypertension, or history of myocardial infarction in the last 12 months;Significant neurologic or psychiatric disorders including dementia or seizures;Active uncontrolled infection (requiring IV antibiotics) or active tuberculosis;Active disseminated intravascular coagulation;Other serious underlying medical conditions which could impair the ability of the patient to participate in the study;Having participated in another clinical trial or having received any investigational agent in the preceding 30 days before study entry;Known allergic/hypersensitivity reaction to any of the components of the treatment;Pregnancy (absence confirmed by serum/urine beta HCG) or breastfeeding;Other active malignancy within 3 years, with the exception of a history of either one of the following, adequately treated: oral cancer, basal cell carcinoma of the skin, pre-invasive carcinoma of the cervix, superficial bladder cancer, carcinoma in situ of the prostate, cervix or breast;Legal incapacity or limited legal capacity;Medical, psychological or socio-geographical conditions or situations which, in the opinion of the investigator, would not permit the patient to complete the study or sign meaningful informed consent;Active, known or suspected autoimmune diseases. Patients with vitiligo, type I diabetes mellitus, residual hypothyroidism due to autoimmune condition only requiring hormone replacement, psoriasis not requiring systemic treatment, or conditions not expected to recur in the absence of an external trigger are permitted to be enrolled;Conditions requiring systemic treatment with either corticosteroids (> 10 mg daily prednisone equivalents) or other immunosuppressive medications within 7 days of study drug administration. Inhaled or topical steroids and adrenal replacement doses > 10 mg daily prednisone equivalents are permitted in the absence of active autoimmune disease.
